#### 8.3.5 ADVERSE EVENT REPORTING

Site coordinators and/or the study team will record potentially related AEs and severe AEs in the electronic data capture (EDC) system, include them in the statistical analysis, and follow the reporting procedures outlined in the trial-specific MOP. The MOP section on reporting severe AEs will encompass the requirements of:

1. Reviewing IRB's policies and procedures
2. Standard Operating Procedures (SOPs) for the Streamlined, Multisite, Accelerated Resources for Trials IRB Reliance platform (SMART IRB)

3. ICH E6(R2), GCP: Integrated Addendum to ICH E6(R1): Guidance for Industry
4. Following local IRB's policies and procedures, when applicable. If there are discrepancies between the procedures, we will follow the most stringent of the procedures.

The DCOC will report severe AEs to the reviewing IRB for its yearly continuing review. The DCOC will report to the Central IRB (cIRB), as specified in the study-specific IRB communication plan, based on recommendations of the SMART IRB. Sites will also report severe AEs to the local IRB, per local IRB policies and procedures, and make them available to the sponsor (DCOC) on a continuing basis through the EDC system. The study team will report to the DSMB, per the DSMB charter.

The trial-specific MOP will describe the details of the reporting structure and additional details related to timelines for reporting.

The specific regulations of the FDA do not apply to this protocol because this is not an FDA-regulated trial.

---

#### 8.3.6 SERIOUS ADVERSE EVENT REPORTING

Site coordinators will record all SAEs in the EDC, and the DCOC will report SAEs, per Table 4 below. The DCOC will notify monitoring personnel (e.g., medical monitor) and monitoring bodies (e.g., DSMB), per the DSMB charter.

**Table – Serious Adverse Event Reporting.**

| Report to                                                      | Timing                                                                    | Notes                                            |
|----------------------------------------------------------------|---------------------------------------------------------------------------|--------------------------------------------------|
| Reviewing IRB (SMART IRB definition)                           | Yearly (minimum)/at continuing review                                     | For continuing review; Submitted to IRB via DCOC |
| Local IRB                                                      | Per local IRB policies and procedures                                     |                                                  |
| DCOC (Sponsor, per SMART IRB definitions, and lead trial team) | Immediately, but no later than 48 hours after finding out about the event | CO-SOP-012.v1.0/SOP                              |
| Overall PIs (per SMART IRB definitions)                        | Immediately, but no later than 24 hours after finding out about the event |                                                  |
| Medical Monitor                                                | Per DSMB charter                                                          |                                                  |
| DSMB                                                           | Per DSMB charter                                                          |                                                  |
| NIH Project Scientist                                          | Per DSMB charter                                                          |                                                  |

All SAEs will be followed until satisfactorily resolved, the site investigator deems the event is chronic, the participant is stable, or the participant is lost to follow-up. The DCOC/trial sponsor may request other supporting documentation, and sites should provide this as soon as possible.

The DCOC will ensure the summary and report of SAE data to the reviewing IRB in time for consideration at the next continuing review. The DCOC will also create and provide any SAE data summaries requested by the

monitors or specified in the DSMB charter. The site investigators will be responsible for following their local institution's requirements.

The trial-specific MOP has additional details.

---

### 8.3.7 REPORTING EVENTS TO PARTICIPANTS

The study team will notify participants of those trial-related (or potentially trial-related) SAEs that may affect their willingness to continue with the trial or the future health of the participant. Any of the following can determine if study personnel should contact participants: the IRB, the medical monitor, the DSMB, or the PIs. The person or oversight body that makes the determination will inform the DCOC, which will instruct the site investigators and site coordinators to contact the participants consented through their site.

Site investigators and/or site coordinators will record any contact with participants, if necessary, in the EDC and/or trial log.

---

### 8.3.8 EVENTS OF SPECIAL INTEREST

We have not identified other reportable events for this trial.

---

### 8.3.9 REPORTING OF PREGNANCY

Given the age of the child participants in this study, pregnancy is unlikely. In the unlikely event pregnancy were to occur, the child would be withdrawn from the study. Child participants' pregnancies will be reported in the EDC but not followed for the pregnancy duration. While the RAMP intervention would not affect a pregnancy in any way, a patient would likely be referred to a psychiatrist or obstetrician for stimulant cessation or management.

---

## 8.4 UNANTICIPATED PROBLEMS

---

### 8.4.1 DEFINITION OF UNANTICIPATED PROBLEMS (UP)

The Office for Human Research Protections (OHRP) considers unanticipated problems involving risks to subjects or others (UPIRTSOs) to be any problem, event, or new information that is:

- Unanticipated or unexpected;
- Related to the research, and
- Involves new or increased risks to subjects or others.

A UPIRTSO is not necessarily an AE or an SAE. For example, a breach of confidentiality is a potential UPIRTSO that is not an AE or SAE.

The trial-specific MOP provides additional details.

#### 8.4.2 UNANTICIPATED PROBLEM REPORTING

Site investigators and/or site coordinators must report potential UPIRTSOs, per this protocol, to the reviewing IRB, via the method(s) specified in the MOP, and directly to the DCOC. If the UAMS IRB determines the issue is, indeed, a UPIRTSO, the DCOC will notify persons and entities as required by UAMS IRB policies and procedures, the study-specific communication plan, and the DSMB charter. Site investigators and/or site coordinators must also report these events to their local institutions according to the rules and regulations of the local institution. The reviewing IRB will report the issue to OHRP, per the policies of the reviewing IRB. For the UAMS IRB, which will be the reviewing IRB for sites in this trial, the required reporting times are provided in the contemporaneous version of 10.2, *Information that must be reported to the IRB and IRB actions*, which is available via <http://irb.uams.edu/irb-policies/current-irb-policies/principal-investigator-responsibilities/>. The reporting times, at the time of the approval of this protocol, are in the table below.

**Table – Unanticipated Problem Reporting** (per UAMS IRB policy at time of approval of this protocol).

| Unanticipated Problem     | Required Reporting Time to UAMS IRB                           |
|---------------------------|---------------------------------------------------------------|
| Death or life-threatening | Immediately to IRB office or IRB Chair                        |
| All other events          | Within 10 days of event or notification of event if non-local |

#### 8.4.3 REPORTING UNANTICIPATED PROBLEMS TO PARTICIPANTS

The participants will be notified of those study-related (or potentially study-related) SAEs and unanticipated problems (UPs) that may affect the participants' willingness to continue with the study or the future health of the child enrolled in the study. This determination can be made by any of the following: the IRB, the medical monitor, the DSMB, or the sponsor. The person or oversight body that makes the determination will inform the DCOC, which will instruct the site PIs/research coordinators to contact those participants enrolled through their site. Contacts with participants, if necessary, will be recorded on the appropriate CRF and/or study log.

## 9 STATISTICAL CONSIDERATIONS

All statistical analyses will be detailed in a separate Statistical Analysis Plan (SAP). This plan may be revised during study implementation to accommodate protocol amendments and to make necessary changes to unexpected issues in study execution and data that impact planned analyses. A finalized SAP will be issued prior to data lock.

### 9.1 STATISTICAL HYPOTHESES

Primary Endpoint:

H1: Use of the RAMP platform will result in significantly greater number of completed **clinical assessments** per participant in the intervention group compared to the control group

### 9.2 SAMPLE SIZE DETERMINATION

A total sample of 36 participants was agreed in accordance with published guidance for pilot studies. Up to 36 caregiver/child dyads and 20 providers will be enrolled. Our proposed sample size is also consistent with the recommendations of Whitehead and colleagues (2016). Their derived new stepped rules of thumb for a pilot trial sample size vary depending on an estimated standardized effect size for the main efficacy trial; therefore, if we assume a medium Cohen's effect (i.e.,  $0.3 \leq \delta \leq 0.7$ ) and 90% power for the main trial, a sample size of 36 participants with 18 randomized to each intervention arm in the pilot study is sufficient.

With a focus on participant recruitment and adherence, a sample size of 36 allows the study team to estimate an expected recruitment rate of 25% and adherence rate of 50%, each within 12-14 percentage points, with a confidence level of 90%. We expect the rate of return of the RAMP Reports to be a comparable rate to the general survey response rate of 52.7%, though it may be higher as the platform aims to function as an engagement tool.

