The entire timeline will span 17 months with three phases. In the first phase of the study, the providers from the participating practices will receive ADHD Best Practices education and training in the portal use, and will be asked to provide informed consent. A member of the clinic staff (nurse, medical assistant or practice manager) will be identified as site champion. The site champion will facilitate communication between the site study team and the clinic staff. The second phase of the study will focus on child/caregiver and provider utilization. Providers will identify patients with a diagnosis of ADHD who are being started on stimulant medication to be contacted by study staff for enrollment. Research coordinators will discuss the study, perform eligibility screening and obtain consent (if deemed eligible by PI). The consented caregiver/child dyads will be randomized to intervention (requests to submit the RAMP Reports for 3 months) or control (usual care with attention control) groups. Families will be approached until 36 caregiver/child dyads are enrolled (only one child in a family may be enrolled). Each practice will have 6 weeks to enroll 9 participants. After the 6 weeks, practices with low enrollment will receive additional supports. Each week, progress to target will be evaluated to determine if any practice needs additional resources. If multiple practices do not meet enrollment goals, the study team may consider relaxing exclusion/widening inclusion criteria (ex. include patients undergoing re-titration, widen age criteria) and/or opening enrollment. Enrollment will be paused for 3 months from the last month of school to the start of the new school year (beginning of May to end of July). This will decrease the burden on practices and study staff during the time of the year with the fewest number of ADHD diagnoses. Once enrolled, caregiver/child participants will be randomized to either the intervention or control group and followed for approximately 3 months. Participants randomized to the intervention group will submit RAMP reports weekly for 4 weeks and then monthly for 2 months. Participants randomized to the control group will receive digital education handouts at the same frequency as the RAMP reports in the intervention arm. Research coordinators will periodically review the child participant's EMR and mark how many paper symptom assessments are returned while enrolled on the study for both groups. Research coordinators will also access the RAMP platform to log RAMP reports returned by caregivers/teachers, RAMP reports reviewed by providers, and provider survey results. All caregiver participants will complete a 90-day Vanderbilt Assessment as a retention measure (see section 1.2.1 for more details). This phase will continue until all 36 participants have completed their 3-month study period. In the third phase, the above endpoints will be calculated, the full-scale trial will be designed, and the findings presented in a manuscript.

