### 5.4 SCREEN FAILURES

The study team will consider the caregiver/child dyads who undergo screening but who do not enroll in the trial to be screen failures, including those who are contacted by the study team but who do not meet inclusion and/or exclusion criteria. Research coordinators must document and retain the reason for screen failure.

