## 6.3 STUDY INTERVENTION COMPLIANCE

The study team will measure and monitor compliance by reviewing the reports submitted by caregivers and teachers and the reports reviewed by providers. The study team will summarize the RAMP utilization as follows:

- Cumulative number of RAMP Reports completed by caregivers
- Cumulative number of RAMP Reports were completed by teachers

- Cumulative number of RAMP Reports were reviewed by providers

The submission of reports will be time-stamped in the REDCap database system. Additionally, caregivers will be asked to provide the diagnostic assessments at study enrollment, and caregivers will be asked to submit a [study assessment](#) at the study end-point (at 90 days).

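### Protocol 9.2 uses n = 36 for both precision figures: wrong for recruitment, and right for adherence only under one reading of a rate that is never defined

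*Protocol*

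**What the plan says.** Section 9.2 first supports 36 dyads by published guidance for pilots, including a rule of thumb under which "a sample size of 36 participants with 18 randomized to each intervention arm in the pilot study is sufficient". It then gives a precision argument: "a sample size of 36 allows the study team to estimate an expected recruitment rate of 25% and adherence rate of 50" percent, "each within 12-14 percentage points, with a confidence level of 90" percent. The sentence after that expects RAMP Reports to be returned at about the general survey response rate of 52.7%, possibly higher.

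The meaning of 36 is fixed elsewhere. Section 4.1: "Families will be approached until 36 caregiver/child dyads are enrolled". Section 9.2: "Up to 36 caregiver/child dyads and 20 providers will be enrolled". Section 5.4 takes "the caregiver/child dyads who undergo screening but who do not enroll in the trial to be screen failures", so they fall outside the 36.

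The protocol does not define the adherence rate. Section 6.3, on compliance, lists counts of RAMP use, beginning with "Cumulative number of RAMP Reports completed by caregivers". It closes by mentioning the diagnostic assessment and the Day-90 study assessment, which are asked of caregivers in general. The activity table in section 1.3 confines RAMP Reports to the intervention arm.

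**The concern.** A half-width for a proportion depends on its denominator. Section 9.2 carries one number, the enrolment target, into two rates that do not obviously share it. Recruitment is enrolled dyads over some larger group. Adherence, if it means use of RAMP, can be observed only in the arm that receives RAMP.

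This is the only quantitative precision statement offered for the sample size; the other support is a rule of thumb. Planners of the full-scale trial could take the recruitment estimate to be half as precise as it will be. Depending on what adherence means, they could also take that estimate to be tighter than the data allow.

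**Working it through.** **Inputs.** Rates of 25% and 50%, n = 36, 90% two-sided confidence (z = 1.645), and 18 dyads per arm, all from 9.2. Enrolment stops at 36 (4.1). Requests per reporter: 4 weekly + 2 monthly = 6, sent to one caregiver and one teacher per intervention child (6.1.1).

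**Formulas.** Wald half-width = z·√(p(1−p)/n). Wilson half-width = z·√(p(1−p)/n + z²/(4n²)) / (1 + z²/n). For clustered requests, n is replaced by 18m / (1 + (m−1)·ICC), where m is the number of requests per dyad.

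**1. The protocol's figure, n = 36 for both rates.**
- 25%: 1.645·√(0.25·0.75/36) = 0.119, or 11.9 points (Wilson 11.6).
- 50%: 1.645·√(0.5·0.5/36) = 0.137, or 13.7 points (Wilson 13.2).

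This is the stated 12-14. The arithmetic is correct for n = 36; the question is whether 36 is the right n.

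**2. Recruitment.** With 36 enrolled and a 25% rate, the denominator is 36/0.25 = 144, whether the rate is taken over families approached, screened or eligible. Half-width: 1.645·√(0.25·0.75/144) = 0.059, or 5.9 points (Wilson interval 19.6% to 31.4%). Allowing for the fact that approaching stops at the 36th enrolment gives the same: 1.645·0.25·√(0.75/36) = 0.059. If 36 were the denominator, a 25% rate would mean 36·0.25 = 9 dyads enrolled, which contradicts the design.

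**3. Adherence, under each reading the text allows.**

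| Reading | Basis | 90% half-width at 50% |
|---|---|---|
| Yes/no measure in both arms (for example Day-90 form return) | 36 dyads | 13.7 points (Wilson 13.2) |
| RAMP adherence, each dyad classed yes/no | 18 dyads | 1.645·√(0.25/18) = 19.4 points (Wilson 18.1; interval 31.9% to 68.1%) |
| RAMP return per request, caregiver and teacher | 18·12 = 216 requests in 18 dyads | 11.6 (ICC 0.3), 14.3 (ICC 0.5), 16.5 (ICC 0.7) |
| RAMP return per request, caregiver only | 18·6 = 108 requests in 18 dyads | 12.5 (ICC 0.3), 14.8 (ICC 0.5), 16.8 (ICC 0.7) |

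The ICC values are assumptions; the protocol gives none.

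**The case against.** **Adherence may be a both-arm measure.** Section 6.3 ends with the Day-90 form, which every caregiver is asked to complete, and section 9.3 uses its completion to define the per-protocol set within all randomized dyads. On that reading 36 is correct and about 14 points stands. The 52.7% for RAMP Reports in 9.2 can also be read as a separate quantity with its own figure. This reading is possible. It is not the most natural one, because the protocol repeatedly assigns that form to retention (1.1, 4.2, 5.5.3, 6.2) and section 6.3 opens with RAMP use. A reader might infer that 36 is the denominator of neither rate, and the documents do not establish that.

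**RAMP return need not have 18 as its denominator.** Counted per request, the half-width can lie close to 14 points. With 12 requests per dyad and an ICC of 5/11 (about 0.45), the design effect is 1 + 11·5/11 = 6 and the effective sample size is 216/6 = 36. A reader might infer that adherence uncertainty is about 40% larger than stated (√2 from halving n). That holds only if each dyad is classed as adherent or not, or if the ICC is 1, and the protocol sets no such classification.

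**The recruitment error is conservative, and nothing turns on either rate.** A true half-width of 6 points does lie within 12. Neither rate is an endpoint: the primary analysis compares counts (9.4.2) and the secondary estimates provider review (9.4.3), each with its own 95% interval. No progression rule uses the 12-14 points. This stands and limits the weight of the point. It does not make the stated figure correct.

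**Conclusion.** The recruitment half is settled. The stated precision of about 12 points should be about 6, assuming the protocol's own 25% and 36 enrolled. No choice of denominator for the recruitment rate makes 36 correct.

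The adherence half is probable, not certain. The text leans towards RAMP Report return, for which the 18 intervention dyads are the sampling units. The half-width is then 18-19 points for a dyad-level yes/no rate, or about 12-17 points per request over the assumed ICC range. About 14 points is directly right only for a yes/no rate measured in all 36 dyads. The defect that can be shown is that the protocol gives a precision for a rate without defining its numerator or denominator.

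Severity is moderate: a figure used to justify the sample size is wrong in one part and undefined in the other, but the size of the trial and its planned analyses do not depend on it.

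**What to change.** In section 9.2:

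- Restate recruitment: with about 144 families approached, a 25% recruitment rate is estimated within about 6 percentage points at 90% confidence. If the rate is taken over screened or eligible families, name that group instead.
- State the numerator and denominator of the adherence rate and give the half-width that matches: about 18-19 points for 18 intervention dyads each classed as adherent or not; a cluster-adjusted figure, with the assumed ICC stated, if counted per request; about 14 points only for a rate measured in all 36 dyads.

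The cost is a sentence or two. Sample size, conduct and participant burden are unchanged. The one drawback is that the adherence figure may become less favourable.

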### 9.3 POPULATIONS FOR ANALYSES

To evaluate completion of clinical assessments and provider acceptability, the study will have two analysis populations:

1. Intention-to-treat (ITT) population – This population will include all participants randomized into the study.
2. Per-protocol (PP) population – This population will include all participants in the ITT population who completed the final **study assessment**.

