| Receive digital handouts (control arm only)                                 | X                     |          |           |
| Allow access to clinical baseline assessment and complete study assessments | X                     |          |           |

|                           |   |  |   |
|---------------------------|---|--|---|
| RAMP platform orientation |   |  | X |
| Best practice education   |   |  | X |
| Review RAMP reports       |   |  | X |
| Complete Provider Survey  |   |  | X |
| Receive Compensation      | X |  | X |

| Participant Activities                                                                 | Day -35—Day 0 | Day 0 | Day 1-28 | Day 29-90  | Day 90
(-30/+15)** |
|----------------------------------------------------------------------------------------|---------------|-------|----------|------------|-----------------------|
| Pre-study visit with provider* (ADHD diagnosis made, stimulant started)                | X             |       |          |            |                       |
| Research coordinator contacts and eligibility screen, principal investigator review    | X             |       |          |            |                       |
| Enrollment and informed consent                                                        |               | X     |          |            |                       |
| Randomized                                                                             |               | X     |          |            |                       |
| Diagnostic Assessment requested from provider                                          |               | X     |          |            |                       |
| RAMP Report request (caregiver and teacher) for intervention group only                |               |       | Weekly   | Monthly*** |                       |
| Digital education handout (control group only)                                         |               |       | Weekly   | Monthly*** |                       |
| Study Assessments (not used in clinical management; retention measure) |               |       |          |            | X                     |

\*Caregiver/child participant dyads will be enrolled within 5 weeks (35 days) of the child being prescribed stimulants.

\*\*The window for the 90-day Study Assessment is -30 days to +15 days. Study Assessments must be received by the study team within this window.

\*\*\*Each monthly period is defined as 28 days.

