#### 4.3 END OF STUDY DEFINITION

The end of the study is defined as the date when all study activities for all participants are completed or determined to be out of window as defined in this protocol.

The study will end for caregiver/child participants after they have reached 90 days post enrollment and either completed their final [study assessment](#) or failed to complete it by Day 105.

The study will end for provider participants after they have completed the provider survey linked to their last enrolled patient's 3-month RAMP report, or failed to complete it within the review window.

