**RAMP Reports completed by caregivers:** The RAMP caregiver interface includes monitoring of ADHD symptoms, engagement in behavioral health care visits, and progress in educational settings. These domains of information have been selected as they are typically combined by providers when making decisions regarding medication dose adjustment. The requests for reports will be sent to caregivers as a link in a text message. Upon clicking the link, they will be able to select radio button responses to questions directly on their mobile device (without any login requirement). The RAMP Report requests will be sent weekly for 4 weeks then every month for the remaining 2 months. RAMP Reports will be submittable for 72 hours after initial release. Once a new RAMP Report is available, caregivers cannot go back and complete reports for prior periods.

**RAMP Reports completed by teachers:** Caregivers in the intervention group will provide teachers with a secure, unique link to access the RAMP Platform. This link will be in the form of a QR code which can be printed on paper or emailed directly to the teacher from the caregiver. Teachers will enter the symptom information directly into the platform. The teacher's RAMP Reports are identical to caregiver RAMP Reports, will consist of the first 18 inattention/hyperactivity questions on the Vanderbilt Assessment, and will be requested at the same interval as the caregivers. We will use an approach similar to that used by Power *et al.* The responses to the teacher RAMP Reports will be available to the providers on the RAMP portal. If a child's teacher does not want to use the RAMP platform, the child will not be disqualified. If a child has multiple teachers, the caregiver should choose one teacher to participate, preferably the one that spends the most time with the child.

[figure not shown]

**Provider Report Review:** Providers will be alerted by their preferred means (text or email) when new caregiver or teacher reports are available for review. While providers will have access to the platform at all times, there will be one provider survey to document review for any given week that there is either a caregiver survey, teacher survey or both to review. .

| Record ID | DDP New Items from RDW    | Basic Demography Form | initial Vanderbilt | clinician review | 1 week RAMP | clinician review | 2 week RAMP | clinician review | 3 week RAMP | clinician review |

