### 7.3 LOST TO FOLLOW-UP

The study team will consider caregiver/child dyad participants lost to follow-up if they do not complete the final [study assessment](#). Those who do not complete any [clinical assessments](#) (RAMP Reports or paper assessments)

will still be included if they complete the final [study assessment](#) as this is an intention to treat analysis. To minimize the number of participants lost to follow-up, the study team will contact participants approximately 1 week, 4 weeks, and 2 months after consent to ensure there are no technology issues.

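### Return of the Day-90 study form alone decides per-protocol status and loss to follow-up, although the primary count does not use the form, and 7.3 conflicts with 9.3 on who is in the intention-to-treat analysis

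*Protocol*

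**What the plan says.** Protocol 9.3 sets up two populations. For ITT, "This population will include all participants randomized into the study". The per-protocol set is "all participants in the ITT population who completed the final" study assessment; no condition on eligibility, delivery of the assigned arm or withdrawal is added.

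Protocol 7.3 uses the same form for loss to follow-up: "The study team will consider caregiver/child dyad participants lost to follow-up if they do not complete the final" study assessment. It goes on to say that dyads with no clinical assessments at all "will still be included if they complete the final" study assessment, and gives the intention-to-treat principle as the reason.

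The form itself is the Day-90 Vanderbilt. Section 1.3 states: "The window for the 90-day Study Assessment is -30 days to +15 days". Section 4.3 closes a dyad out once it has reached 90 days and has either returned the form or "failed to complete it by Day 105". Sections 1.1, 4.2, 5.5.3 and 6.2 describe the form as a retention marker.

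The primary endpoint comes from elsewhere. RAMP Reports are time-stamped in the platform (8.1), paper assessments are counted by chart review in both arms (4.1), and 9.4.2 leaves study assessments out of the count.

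**The concern.** A per-protocol set normally keeps participants who received what they were assigned and whose endpoint could be observed. Loss to follow-up normally means that the endpoint can no longer be observed. Here neither follows. One form, not needed for the primary count, settles both.

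Three things are at stake. First, dyads with a complete primary count can be reported as lost and dropped from the per-protocol set. Second, returning the study form and returning clinical forms are similar behaviors, so a set chosen on the first may be enriched for the second. Third, 7.3 and 9.3 can be read as giving different ITT populations. The pilot exists to supply utilization and engagement figures for a full-scale trial (3, 9.4.2), so misclassified follow-up would carry forward into that planning.

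**Working it through.** The point is one of definition, so the main check sets the sections side by side. The arithmetic covers the window and an illustration of size.

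**1. Window.** The target is Day 90 with -30/+15 days (1.3). 90 + 15 = 105, which reproduces the close-out day in 4.3. 90 - 30 = 60, so a form can count from Day 60.

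**2. Reports possible per RAMP dyad.** Section 6.1.1: "The RAMP Report requests will be sent weekly for 4 weeks then every month for the remaining 2 months". That is 4 + 2 = 6 requests. With caregiver and teacher each asked, 6 x 2 = 12 reports.

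**3. Classification under the written rules.**

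| Dyad | Primary count complete? | Form returned? | 7.3 | 9.3 per-protocol |
|---|---|---|---|---|
| RAMP, 12 of 12 reports | Yes | No | Lost | Out |
| Control, all paper forms in the chart | Yes | No | Lost | Out |
| Either arm, zero assessments, observed to Day 90 | Yes (count is 0) | Yes | Not lost | In |

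The first two rows are the defect. The third is not: a count of zero is a valid value when use is the endpoint.

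**4. ITT wording.** Section 9.3 has one condition, randomization. Section 7.3 ties inclusion to the form and cites intention to treat. Under 9.3 a dyad with no clinical assessments and no form is in ITT with a count of zero. Under a literal reading of 7.3 it is not.

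**5. How many could be misclassified (assumed inputs).** Take 18 RAMP dyads and read the 50% adherence rate in 9.2 as 9 users and 9 non-users.
- Form returned by 90% of both: per-protocol = 18 x 0.90 = 16.2; users called lost = 9 x 0.10 = 0.9.
- Form returned by 80% of users and 30% of non-users: per-protocol = 9 x 0.80 + 9 x 0.30 = 9.9; users called lost = 9 x 0.20 = 1.8.

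**6. Possible shift of the RAMP mean (assumed inputs).** Suppose 9 engaged dyads average 9 reports and 9 others average 3. The all-randomized mean is (9 + 3)/2 = 6.0. With return rates a (engaged) and b (others), the per-protocol mean is (9a x 9 + 9b x 3)/(9a + 9b).
- a = b = 0.90: (72.9 + 24.3)/16.2 = 6.0, no shift.
- a = 0.90, b = 0.60: (72.9 + 16.2)/13.5 = 6.6, +10%.
- a = 0.95, b = 0.50: (76.95 + 13.5)/13.05 = 6.93, about +15%.

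The same selection acts in the control arm to an unknown degree. The bias in the between-arm difference is the RAMP shift minus the control shift, so neither its size nor its sign can be given.

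**The case against.** The strongest defense is that little rests on the per-protocol set. ITT is all randomized in 9.3, and no primary or secondary result in 9.1, 9.4.2 or 9.4.3 is tied to the per-protocol set. The form also has a rationale: it is the one scheduled study form common to both arms and does not depend on RAMP use, and a chart with no paper forms cannot show whether a control family is still reachable. This stands, and it limits the point. It supports the form as a retention measure, not as the definition of a lost endpoint. The sentence in 7.3 may also be meant only to reassure that non-users are kept; if so, it needs rewording, because it attaches a condition that 9.3 does not have.

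A reader might infer more than the protocol supports:
- *Non-users in the per-protocol set are an error.* They are not. Use is the endpoint, so removing non-users would select on the outcome.
- *A family that returns the form at Day 60 and then withdraws is counted as retained.* Section 7.2 classes it as early-terminated, 4.3 requires 90 days to be reached, and 9.4.8 tabulates completers and discontinuations. All that remains is that such a dyad still meets the per-protocol wording.
- *An early form costs the last 30 days of counting.* Returning the form stops no counting; only withdrawal does.
- *The final RAMP request falls after Day 60.* With 28-day months and weekly requests ending on Day 28, it would fall on Day 84, but the protocol fixes no request days. Monthly requests on Days 29 and 57 would all precede Day 60.

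**Conclusion.** The point holds in this form. The form is the sole criterion for per-protocol status and for loss to follow-up, it is not endpoint data, and dyads with full endpoint data can be called lost and dropped. This follows from the text without any assumption. Sections 7.3 and 9.3 must also be reconciled on ITT.

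The reach is limited. If 9.3 governs, the all-randomized result is untouched and the effect is confined to the per-protocol and disposition or retention results. Figures of about 1 to 2 of 9 RAMP users called lost, and a RAMP per-protocol mean 0 to 15% above 6.0, are illustrations that rest on assumed engagement and return rates. They do not show that the per-protocol mean will be inflated, and they say nothing about the between-arm difference. If 7.3 were applied literally, the ITT analysis would be exposed to the same selection. The change is worth making because it is cheap and the pilot's follow-up figures will be reused.

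**What to change.** **Section 7.3.** State that every randomized dyad is in the ITT analysis whether or not the form is returned. Define loss to follow-up for the primary endpoint as platform or chart data that cannot be observed through the 3-month count.

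**Section 9.3.** Choose one of two:
- Define per-protocol by eligibility, delivery of the assigned arm by the study team (RAMP requests sent, or handouts sent) and an endpoint observable over the count period. Require neither the form nor any RAMP use.
- Keep the present set, rename it study-assessment completers, and treat it as supportive only.

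**Reporting.** Give Day-90 form return as a separate retention measure, alongside withdrawal status at Day 90.

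The definition should not require that a family activated its RAMP link, and should not make withdrawal an exclusion in its own right. Under 7.2 a confirmed opt-out from RAMP texts leads to withdrawal, while control handouts go by email (6.1.1), so both conditions would select on engagement in one arm. Some of this asymmetry survives under the first option if counting stops at withdrawal, which is a further reason to keep the set supportive.

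**Cost.** Wording in the protocol, carried into the SAP. Timestamps, chart counts and withdrawal dates are already planned, and 8.1 has coordinators verify that RAMP requests went out. The protocol does not say that handout delivery is logged, so this should be confirmed. The per-protocol set will be close to ITT and so less informative as a contrast.
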